### Incidence of Adverse Events

The patients will be requested to freewill report any acupuncture-related adverse event (AEs). AEs will be recorded and evaluated by the researchers. Acupuncture-related AEs may include bleeding, local infection, soreness, sweating, and so on.

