## Abstract

**Background:** Acupuncture has been clinically used to treat epilepsy after stroke. However, most of the current clinical studies are observational studies, and there are few well-designed randomized controlled trials (RCTs). Hence, we designed a multicentre RCT to assess the advantages and efficacy of acupuncture for post-stroke epilepsy (PSE).

**Methods/Design:** This is a two-arm, parallel, participants-blinded and assessor-blinded and multicentre RCT. A total of 120 patients with PSE aged from 18 to 75 years will be randomly assigned to two groups (routine treatment plus acupuncture group and routine treatment plus sham acupuncture group) at a 1:1 ratio. The participants will perform acupuncture or sham acupuncture treatment three times a week and be ongoing 8-week treatment. The primary endpoint is the proportion of seizure-free patients. A safety profile will be established. We will record adverse events for the safety evaluation.

**Discussion:** The study will provide high-quality clinical evidence on the effectiveness and safety of acupuncture for treating patients with epilepsy after stroke.

**Clinical Trial Registration:** Chinese Clinical Trial Registry, identifier: ChiCTR2100046114.

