## Introduction

Stroke is a common cause of epilepsy in adults, causing about 10% of all epilepsy and 55% of newly diagnosed seizures in older adults (1). Although recent advances in the diagnosis and treatment of acute stroke have increased patient's life expectancy, the incidence of Post-stroke epilepsy (PSE) is also on the rise (1). PSE is defined as unprovoked epileptic seizures at least 1 week after stroke and occurs in at least 4-6% of the stroke patients (2). PSE is one of the major complications after stroke. A meta-analysis found that younger age, hemorrhagic component, and cortical involvement at stroke onset were associated with a higher risk of PSE (3). PSE may be associated with increased mortality and unfavorable outcomes. In addition, there is a high risk of seizure recurrence following an unprovoked seizure after a stroke. Although the European Stroke Organization guidelines recommend that treatment with antiepileptic drugs (AEDs) should be considered after one unprovoked seizure (4), there is currently limited evidence on the efficacy and safety of AEDs for PSE (1, 4, 5). The management of PSE is also challenged by several factors, such as the changes in pharmacodynamics due to older age, co-morbidities, and co-medications in stroke survivors. Older people, in particular, may be more susceptible to side effects from antiseizure medications (5).

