**Outcomes**					
The proportion of seizure-free patients			×	×	×
The time recurrence to the first seizure			×	×	×
The proportion of completed diary entries			×	×	×
Mini-mental status examination		×	×	×	×
Montreal cognitive assessment		×	×	×	×
Activities of daily living		×	×	×	×
EEG assessment		×	×	×	×

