**Safety**					
Adverse events		×	×	×	

*× represents the beginning of information collection*.

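### Adverse events are requested only as voluntary reports of needling-related events and scheduled only to week 8, so other and later events are not systematically captured for the promised safety profile

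*Protocol article*

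**What the plan says.** The protocol article deals with safety in four places.

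- **Incidence of Adverse Events.** The request to patients is: "The patients will be requested to freewill report any acupuncture-related adverse event". The section then says "AEs will be recorded and evaluated by the researchers". Its examples are all effects of needling: "Acupuncture-related AEs may include bleeding, local infection, soreness, sweating, and so on".
- **Table 1, Safety.** The row "Adverse events" is marked at day 0, week 4 and week 8. The run-in and 1-year cells are empty. The footnote says that the mark "represents the beginning of information collection". In the outcomes part of the same table, every row, including "The proportion of seizure-free patients", is marked at 1 year.
- **Abstract, Methods/Design.** "A safety profile will be established". The next sentence says that adverse events will be recorded for the safety evaluation, without limiting them to acupuncture.
- **Introduction, and Interventions and Comparison.** The Introduction notes that post-stroke epilepsy may carry increased mortality, and warns: "Older people, in particular, may be more susceptible to side effects from antiseizure medications". Both groups are then given AEDs, started together with the needling.

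**The concern.** A safety comparison between randomised arms needs all events, asked for in the same way in both arms, with cause judged afterwards. Here the request to the patient already contains a causal judgement. Someone with drowsiness, a fall, a rash or a hospital admission has little reason to volunteer it as an effect of acupuncture, and no questioning that would bring it out is described.

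The schedule adds a second gap. The primary outcome runs to 12 months and the article plans a 1-year contact with every patient, but adverse events are not scheduled there. A death or a non-seizure admission in month 6 therefore has no defined place in the safety data.

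At stake is whether the published safety statement describes what happened to the patients or only what they chose to report as a needling effect during the first 8 weeks.

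**Working it through.** **No figure to reproduce.** The article gives no expected adverse event rate and no capture rate. The check is therefore a comparison of the text, followed by an illustration on stated assumptions.

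**1. The request against the promise**

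| Place | Scope of adverse events |
|---|---|
| Abstract | All adverse events, plus a safety profile |
| Incidence of Adverse Events, request to patients | Voluntary, acupuncture-related only |
| Incidence of Adverse Events, researchers' role | Record and evaluate; no qualifier, no questioning described |
| Table 1 | Day 0, weeks 4 and 8 |

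The narrow request and the broad promise do not match. The only stated route from patient to record is the narrow one.

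**2. Window**

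- Scheduled adverse event assessment ends at week 8. If the 1-year contact is counted from baseline, coverage is 8/52 = 15.4%, which leaves 1 − 8/52 = 84.6% of follow-up without a scheduled assessment.
- If the year is counted from the end of treatment, coverage is 8/(8 + 52) = 8/60 = 13.3%.
- Under Secondary Outcomes, the 1-year contact is said to collect the time and frequency of occurrences, which in context means seizures. Adverse events are not named.

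**3. Illustration of under-capture**

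Inputs:

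- n = 60 per arm, from 120 patients randomised 1:1 (Abstract).
- True proportion p of patients with a given event: assumed.
- Probability c that such an event reaches the record: assumed, equal for all patients, and independent between patients.

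Formulas: expected recorded events = n·p·c; P(at least one recorded) = 1 − (1 − p·c)^60.

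For p = 5%:

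- c = 1: 60 × 0.05 = 3.0 expected; 1 − 0.95^60 = 0.954
- c = 0.75: 2.25 expected; 1 − 0.9625^60 = 0.899
- c = 0.50: 1.5 expected; 1 − 0.975^60 = 0.781
- c = 0.25: 0.75 expected; 1 − 0.9875^60 = 0.530

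P(at least one recorded) over a range of p:

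| True rate p | c = 1 | c = 0.75 | c = 0.50 | c = 0.25 |
|---|---|---|---|---|
| 2% | 0.702 | 0.596 | 0.453 | 0.260 |
| 5% | 0.954 | 0.899 | 0.781 | 0.530 |
| 10% | 0.998 | 0.991 | 0.954 | 0.781 |

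The loss matters most for the less common events. At 10% or more, an event would probably be seen at least once even with poor capture, but its recorded frequency would still be too low by the factor c.

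**The case against.** **The researchers also record events.** The section says that adverse events will be recorded and evaluated by the researchers, the Abstract repeats this without a causal filter, and Table 1 sets fixed time points. A reader might infer from the request to patients that nothing else is collected, or that the patient has the last word on causality. The text supports neither. Some other events may well be recorded, and the final evaluation belongs to the researchers. What stands is that no systematic route for those events is described, and that the patient's view filters what is volunteered.

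**The window covers the needling.** Treatment ends at week 8, and bleeding, soreness and local infection are acute effects. The footnote describes the mark as the beginning of collection, so later recording is not strictly ruled out. This is fair for needling effects. It does not explain why the 1-year cell is empty only in the safety row, and it does not cover drug-related events or deaths.

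**Late seizures are followed.** A reader might infer that status epilepticus after week 8 would be lost. It would probably surface through the seizure outcome, which runs to 12 months. The gap concerns deaths, non-seizure admissions and other serious events.

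**Reporting that differs by arm.** Because patients hear one option described as less painful, a reader might infer that the filter works differently in the two arms. The article says patients are told they may get either type and are blinded to which one. The label alone does not show differential reporting; that would need unblinding, which the documents do not establish.

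**Condensed article.** The questioning script and the serious event procedures may be in the full protocol, and the Figure 1 legend mentions a data monitoring committee. Their absence is not the point here. The point is what the article does fix: a voluntary request, a causal limit, and a last scheduled assessment at week 8.

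**Conclusion.** The point holds as a weakness in a stated rule. Followed as written, the request and the schedule do not systematically capture AED-related events, events the patient does not link to needling, or deaths and non-seizure hospitalisations after week 8. The likely direction is that absolute incidence is understated. The size cannot be derived from the document; the probabilities above depend entirely on the assumed rates and capture fractions.

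A reader might also want to express the size as an upper limit after zero events. With 60 patients that one-sided 95% limit is 1 − 0.05^(1/60) = 4.9% even with perfect collection, so it reflects the sample size and not this defect. Dividing it by a single assumed capture rate would give a figure with no support in the document.

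This should be changed, but it does not affect the efficacy analysis.

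**What to change.** 1. Bring the section on adverse events into line with the Abstract: record all adverse events regardless of perceived cause.
2. Ask one standard open question, worded identically in both arms, at the existing week 4 and week 8 visits.
3. Have causality judged afterwards by a researcher blinded to the arm.
4. Record serious adverse events and deaths at the existing 1-year contact, and mark that cell in Table 1.
5. Report all-cause events and acupuncture-related events separately, by arm.

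The cost is a revised and slightly longer form, a few minutes at contacts that already take place, and more unrelated events to record and classify. No extra visit is needed and treatment does not change. It is best done before patients are enrolled, because events that were not recorded at the time cannot be reliably recovered later.

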### Data Collection and Management

We will gather basic information, disease severity assessment, and chemical examinations. The investigator will fill in the data separately in the case report forms (CRFs) and research medical record. Based on the need for data traceability, the original information will be saved in the study of medical records. CRF is designed to convenient for data entry input. Participants are identified by a code and their personal information is not displayed.

### Statistical Analysis

The researchers of Tianjin University of TCM will perform statistical analysis, and they will analyze the data using SAS 9.3 software. Statistical analysis is conducted by researchers with statistical qualifications. Results data will be analyzed in accordance with the intent-to-treat principle, including all patients after baseline assessment, regardless of whether they received treatment or not. Statisticians will use descriptive statistics to summarize the demographic characteristics of the two groups. We will describe continuous variables in terms of mean and standard deviation, and use the *t*-test. Categorical variables will be undertaken using the χ2 test.

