### Outcome Measures

#### The Primary Outcome

The primary endpoint will be defined as the appearance of a second seizure under treatment or by finishing the 12-month follow-up period without seizures (29, 35).

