#### Secondary Outcomes

Secondary outcomes will include the time recurrence to the first seizure. An event is defined as the time of the first relapse of a seizure after baseline; the time of the seizure is calculated as the difference of weeks between the date of the visit identifying the crisis and the date of the baseline visit. The differences in cognitive functions and quality of life, which will be estimated using the Mini-Mental Status Examination (36), Montreal Cognitive Assessment (37), the Activities of daily living (ADL) (38) and EEG assessment. EEG examinations will be performed at the beginning of the study, during the treatment and follow-up period. Assessments will be conducted by a researcher, who is unaware of the treatment to which the participant is assigned. To evaluate compliance with treatment, the proportion of completed diary entries over the 8-weeks research period will be calculated.

The outcomes will be evaluated at weeks 0, 4, 8, and 12 months. To assess the long-term prognosis, we will follow up with all patients 1 year later through clinic visits, home visits, social media, or telephone contact to collect data on the time and frequency of their occurrence.

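### The article's only rule for a numeric outcome is the t-test; read as written it would cover time to first seizure, a censored secondary outcome that the t-test cannot handle properly

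*Protocol article*

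**What the plan says.** The Statistical Analysis section sets two rules. For numeric data: "We will describe continuous variables in terms of mean and standard deviation", followed by the t-test. For the rest: "Categorical variables will be undertaken using the χ2 test". No other test is named anywhere in the article. The same section commits to intention to treat, "including all patients after baseline assessment, regardless of whether they received treatment or not".

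Under Secondary Outcomes: "Secondary outcomes will include the time recurrence to the first seizure". The event is tied to a relapse: "An event is defined as the time of the first relapse of a seizure after baseline". Its timing is a number of weeks, "calculated as the difference of weeks between the date of the visit identifying the crisis and the date of the baseline visit". The visit schedule is sparse: "The outcomes will be evaluated at weeks 0, 4, 8, and 12 months". The same section also says that the one-year follow-up will collect when, and how often, seizures occurred.

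Under The Primary Outcome, the article expects some patients to reach the endpoint "by finishing the 12-month follow-up period without seizures". It gives no censoring rule and names no method for censored data.

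**The concern.** A patient who completes 12 months without a seizure, or who is lost before having one, has no time to first seizure. All that is known is that it exceeds the time observed. A t-test needs a number for every patient it includes, so the analyst must either leave these patients out or give them their follow-up time as if a seizure had happened then.

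Leaving them out selects patients on a post-randomisation result and removes the very patients in whom treatment worked. Using follow-up time counts a dropout as a relapse on the day of dropout. If the rule stays as written, that choice could be made after the data are seen.

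**Working it through.** **Inputs from the article.** 120 patients randomised 1:1, so 120 / 2 = 60 per arm; follow-up of 12 months, taken as 52 weeks; visits at weeks 4 and 8 and at 1 year. The article gives no relapse rate, effect size, dropout rate or power for this outcome, so there is no figure of its own to reproduce.

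**Assumptions.** Exponential seizure times, two-sided 5% tests, and 2,000 to 4,000 simulated trials per scenario. Seizure-free rates at 12 months, hazard ratios and dropout rates are assumed.

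**Step 1: what each t-test compares.** Take 50% (sham) versus 70% (acupuncture) seizure-free. With S the 12-month seizure-free proportion, the hazard is h = −ln(S)/52, so 1/h = 52/0.6931 = 75.0 weeks and 52/0.3567 = 145.8 weeks. Expected relapses are 60 × 0.50 + 60 × 0.30 = 48, so 72 of 120 patients (60%) have no event time.

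- Relapsers only: the mean is 1/h − 52·S/(1−S). Sham: 75.0 − 52.0 = 23.0 weeks. Acupuncture: 145.8 − 121.3 = 24.5 weeks. The arms differ by about 1.4 weeks although relapse falls from 50% to 30%.
- Seizure-free patients set to 52 weeks: the mean is (1−S)/h. Sham: 0.5 × 75.0 = 37.5. Acupuncture: 0.3 × 145.8 = 43.7. The difference is about 6.2 weeks. With complete follow-up this is a legitimate restricted mean.

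**Step 2: power with complete follow-up and exact dates.**

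| Assumed scenario | Log-rank | t-test, relapsers only | t-test, follow-up time as seizure time |
|---|---|---|---|
| 60% seizure-free on sham, HR 0.5 | 0.551 | 0.058 | 0.458 |
| 50% on sham, HR 0.5 | 0.647 | 0.060 | 0.557 |
| 50% vs 70% | 0.62 | 0.07 | 0.54 |
| 40% vs 65% | 0.81 | 0.08 | 0.73 |
| 60% vs 80% | 0.69 | 0.06 | 0.58 |

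Check on the log-rank column by Schoenfeld's formula at 50% vs 70%: HR = ln(0.7)/ln(0.5) = 0.515; z = √(48/4) × |ln 0.515| − 1.96 = 3.464 × 0.664 − 1.96 = 0.34; power = Φ(0.34) = 0.63, against 0.62 simulated.

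At HR 0.5 the second t-test loses 0.551 − 0.458 = 0.093 and 0.647 − 0.557 = 0.090, about 9 points.

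**Step 3: dropout, no true effect.** When follow-up time is used as seizure time:

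| Assumed dropout by arm | Type I error, 50% seizure-free | Type I error, 70% seizure-free |
|---|---|---|
| 0% vs 0% | 5% | not run |
| 10% vs 20% | 8% | 11% |
| 5% vs 35% (extreme) | 37% | 59% |

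The log-rank test stays near 5% throughout.

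**Step 4: dating by visit.** Under the article's definition, a relapse after week 8 is normally identified at the 1-year visit and gets about 52 weeks, the same value as a seizure-free patient. At 50% vs 70%, the proportion relapsing by week 8 is 1 − 0.5^(8/52) = 10.1% on sham and 1 − 0.7^(8/52) = 5.3% on acupuncture. The other 50 − 10.1 = 39.9% and 30 − 5.3 = 24.7% relapse later and are dated at week 52. So about 80% of relapses (39.9/50 and 24.7/30) tie with seizure-free patients. The t-test then sees 89.9% versus 94.7% of patients at 52 weeks. Simulated power is 0.17 at 50% vs 70%, and 0.17 to 0.23 over the three pairs in the table. A log-rank test that keeps event status has 0.61 to 0.80.

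**The case against.** The strongest reply is that the article never says time to first seizure will be compared by a t-test. The test sentences follow directly after one on demographic characteristics and could be read as generic or as baseline comparisons. The Secondary Outcomes section describes this outcome in event terms. A condensed article may leave the survival method to a full protocol or SAP not shown here, and silence alone would be no finding. This stands as a limit: the assignment to the t-test is an inference. It does not remove the point, because the section opens with how the results will be analysed and then states a rule. That rule is the only one a number of weeks can fall under, and it does not suit this outcome.

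A reader might take 6% as the expected power. The documents do not support that: excluding every seizure-free patient would contradict the stated intention-to-treat set, and no such exclusion is proposed. It is a worst case. The other route, with complete follow-up and exact dates, keeps its type I error and loses only about 9 points of power.

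A reader might also infer that the trial's main result is at risk. It is not. The primary outcome is a seizure-free proportion, which the chi-square test suits. In the two HR 0.5 scenarios, chi-square at 12 months has power of 0.546 and 0.642, almost the same as log-rank (0.551 and 0.647).

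Finally, the largest type I errors rest on an extreme dropout imbalance. The milder 10% versus 20% case is the fairer guide.

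**Conclusion.** The concern holds at moderate severity. Read as written, the rule for numeric variables covers a secondary outcome that is censored in every seizure-free or lost patient, and both ways of applying a t-test are unsuitable. Restriction to relapsers is the worst case, with power of about 6% at HR 0.5. Using follow-up time as seizure time is close to acceptable only with complete follow-up and exact dates. Its main weaknesses are unequal dropout and the article's own visit dating, the latter leaving power of about 17% at 50% versus 70% seizure-free.

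Every power and error figure rests on assumed relapse, effect and dropout rates with exponential times. The direction of the problem does not depend on them. The documents do not support saying that a t-test has been expressly specified for this outcome, or that the primary comparison is compromised.

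**What to change.** In Statistical Analysis, state that time to first seizure is exempt from the t-test rule. It will be summarised by Kaplan-Meier curves and compared by log-rank test, with a Cox hazard ratio and 95% confidence interval. Patients without a seizure will be censored at the last date on which their seizure status was known.

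In Secondary Outcomes, replace the visit date with the actual seizure date, which the planned collection of seizure timing should make obtainable. Where only the interval between visits is known, use an interval-censored or discrete-time method. A survival method without this second change would still give curves that step only at the scheduled visits.

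The cost is a few sentences in two sections and slightly more analysis work in standard SAS procedures. No extra patients or visits are needed. The wording should be settled before unblinding.

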## Methods and Analysis

### Study Design

A multicentre randomized controlled trial (RCT) will be conducted at the Tianjin Nankai Hospital, Tianjin Rehabilitation and Convalescence Center of PLA, Tianjin Gong An Hospital, The Second Hospital Affiliated to Tianjin University of TCM, all of which are teaching hospitals. The protocol was registered with the China Clinical Trial Registry (item number: ChiCTR2100046114), and this study protocol has been approved by the Ethics Committee of Tianjin Gong An Hospital (item number: 2020003). A total of 120 participants will be recruited. All participants will provide written informed consent at the time of recruitment. PSE participants will be recruited and randomly assigned to either conventional therapy plus acupuncture or conventional therapy plus sham acupuncture. The evaluator will evaluate and analyze the results at four points (before treatment, 4 weeks, 8 weeks, and 1 year). Tianjin University of TCM will be responsible for data management and statistics. The flow chart of the trial is illustrated in Figure 1, and Table 1 shows the schedule of measurements.

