### Randomization and Blinding

Randomization will be computer-generated by independent researchers using SAS 9.3 (SAS Institute Inc., Cary, NC, USA) software. Researchers will place the generated list of random numbers into sequentially numbered, opaque, sealed envelopes. Based on the information received from the envelope, consecutive participants will be randomly assigned in a 1:1 ratio to acupuncture group (AG) or sham acupuncture group (SAG). Acupuncturists will be appointed to perform the acupuncture for both groups separately. The research coordinator will not be involved in assessment or treatment. And they will notify the patients that they would be likely to receive either a “less-painful acupuncture developed especially for this study” (sham) or a “traditional Chinese acupuncture” (true). All patients and statisticians will be blinded to group assignments.

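### MMSE, MoCA and ADL have a week-0 score, but the only test named for continuous variables is a t-test with no baseline covariate: valid, but less precise than a baseline-adjusted comparison

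*Protocol article*

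**What the plan says.** **Method.** In Statistical Analysis the protocol article states "We will describe continuous variables in terms of mean and standard deviation" and names the t-test. Categorical variables get a chi-squared test. Nothing is said of ANCOVA, a mixed model, a covariate or a change score.

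**Outcomes concerned.** Under Secondary Outcomes: "The differences in cognitive functions and quality of life, which will be estimated using the Mini-Mental Status Examination", followed by MoCA, ADL and EEG.

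**Timing.** The same section says "The outcomes will be evaluated at weeks 0, 4, 8, and 12 months". Study Design agrees, with "four points (before treatment, 4 weeks, 8 weeks, and 1 year". In Table 1 the rows for MMSE, "Montreal cognitive assessment" and ADL each carry four marks (day 0, 4 weeks, 8 weeks, 1 year). A baseline score is therefore planned for all three scales.

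**Hypothesis.** The last paragraph of the Introduction expects acupuncture to do better than sham on symptoms, cognition and quality of life.

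**Size.** "A total of 120 participants will be recruited" (Study Design), and "consecutive participants will be randomly assigned in a 1:1 ratio to acupuncture group (AG) or sham acupuncture group (SAG" (Randomization and Blinding), which gives 60 per arm.

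**The concern.** A two-sample t-test has no place for a covariate. The plan collects a week-0 score on each scale, and the one test it names does not adjust for that score. When baseline and follow-up scores are correlated, part of the spread between patients at follow-up could be predicted from their starting level. An unadjusted comparison leaves that spread in the error term.

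With 60 per arm and no mention of balancing the arms on cognition, the cost is a wider confidence interval and less power for two of the three domains in the trial's hypothesis. The seizure endpoint is not affected. The article names the t-test, so this questions a stated choice and not merely a detail left to an analysis plan.

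**Working it through.** **No figure to reproduce.** The article gives no significance level, power, effect size, standard deviation or correlation for these scales, so only relative precision can be computed.

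**Inputs**
- n = 120 / 2 = 60 per arm (Study Design; Randomization and Blinding).
- Baseline-to-follow-up correlation rho: assumed, 0.3 to 0.8.
- Same SD at baseline and follow-up, and a two-sided 95% level: assumed.

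The text does not say whether follow-up scores or changes are tested, so both are worked out.

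**Variance of the difference between arms, in units of SD²**
- t-test on follow-up scores: 2/n
- t-test on change scores: (2/n) × 2(1 − rho)
- ANCOVA on the baseline score: (2/n) × (1 − rho²)

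**Ratios**
- ANCOVA to follow-up t-test: 1 − rho²
- ANCOVA to change-score t-test: (1 − rho²) / [2(1 − rho)] = (1 + rho)/2
- Equivalent patients per arm: 60 divided by the ratio

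Example at rho = 0.7. Follow-up scores: 1 − 0.49 = 0.51, a cut of 49%, and 60/0.51 = 118. Change scores: 1.7/2 = 0.85, a cut of 15%, and 60/0.85 = 71.

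| rho | Follow-up scores: ratio, cut | Equivalent per arm | Change scores: ratio, cut | Equivalent per arm |
|---|---|---|---|---|
| 0.3 | 0.91, 9% | 66 | 0.65, 35% | 92 |
| 0.5 | 0.75, 25% | 80 | 0.75, 25% | 80 |
| 0.7 | 0.51, 49% | 118 | 0.85, 15% | 71 |
| 0.8 | 0.36, 64% | 167 | 0.90, 10% | 67 |

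**Interval half-widths.** For follow-up scores the half-width is t(118 df) × sqrt(2/60) = 0.362 SD. For change scores this is multiplied by sqrt(2(1 − rho)). For ANCOVA it is t(117 df) × sqrt(2/60) × sqrt(1 − rho²) × sqrt(1 + 1/116), where the last factor is a small-sample correction.

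| rho | Follow-up t-test (SD) | Change t-test (SD) | ANCOVA (SD) | Follow-up / ANCOVA | Change / ANCOVA |
|---|---|---|---|---|---|
| 0.3 | 0.362 | 0.428 | 0.346 | 1.044 | 1.235 |
| 0.5 | 0.362 | 0.362 | 0.314 | 1.150 | 1.150 |
| 0.7 | 0.362 | 0.280 | 0.259 | 1.394 | 1.080 |
| 0.8 | 0.362 | 0.229 | 0.218 | 1.659 | 1.049 |

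**Checks**
- At rho = 0, ANCOVA gains nothing over the follow-up t-test (width ratio 0.996).
- With 48 per arm (an assumed 20% loss) the follow-up ratios barely move: 1.042, 1.148, 1.393 and 1.657.
- A simulation of 4,000 trials at each of rho 0.3, 0.5 and 0.7 gave standard-error ratios of 1.04, 1.13 and 1.40 for follow-up scores and 1.25, 1.15 and 1.08 for change scores, in line with the formulas.

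**Power for an illustrative difference of 0.5 SD (assumed).** The follow-up t-test has 78% at any rho. The change-score t-test has 64%, 78% and 94% at rho 0.3, 0.5 and 0.7. ANCOVA has 82%, 89% and 97%.

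**The case against.** **The t-test sentence may describe baseline tables only.** It comes straight after the sentence on demographic characteristics and names no outcome. But it speaks of continuous variables without restriction and is the only method given for any of them. If it covered baseline tables alone, the article would name no method at all for the three scales. The recommendation is the same either way.

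**The t-test may be on change from baseline.** Secondary Outcomes speaks of differences and includes a week-0 measurement, so this reading is open. It is a fair limit: one cannot say that the plan throws the baseline away, and the equivalents of 118 and 167 per arm belong to the follow-up-score reading alone. On change scores the gain at rho 0.7 and 0.8 is modest (15% and 10%). ANCOVA is still the more precise at every rho in the range.

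**The correlation is not in the document.** This stands. At rho 0.3 the follow-up t-test interval is only about 4% wider. Rho may also differ by visit, and could well be lower at 1 year than at 4 weeks. The direction of the result is firm; its size is conditional.

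**Three stronger readings are tempting, and the document does not support them.**
- That a chance baseline gap would bias the result. Allocation is random, so the t-test is unbiased on average and its type I error already allows for chance imbalance.
- That each visit will be tested separately on complete cases. The article says nothing of complete cases; it states intention to treat for all patients after baseline assessment. Handling of missing data and repeated visits may properly sit in the analysis plan.
- That a main time point such as week 8 should have been named. The article lists the visits without ranking them, and the choice is ordinary analysis-plan content.

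**Conclusion.** The point holds as a matter of efficiency. The stated t-test is valid, and the article contains no false statement here, but baseline adjustment is more precise under either reading and nothing else in the article supplies it. Across an assumed rho of 0.3 to 0.8, the t-test interval is about 4% to 66% wider than the ANCOVA interval if follow-up scores are tested, and about 24% down to 5% wider if changes are tested. The two readings agree at rho 0.5, where the interval is 15% wider. These sizes rest on the assumed rho, equal SDs at the two visits, and 60 analysed per arm. The point is a free improvement, for secondary outcomes only; it does not threaten the validity of the trial or touch the seizure endpoint.

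**What to change.** In Statistical Analysis, state that MMSE, MoCA and ADL will be compared between groups by ANCOVA with the week-0 score of the same scale as covariate, or by a mixed model for repeated measures that includes that score. Report adjusted differences with 95% confidence intervals, and keep the t-test for unadjusted description only. The remaining model terms and the choice of time point can be left to the analysis plan.

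The cost is a change of wording, best made before unblinding. No extra patients, visits or measurements are needed, because the week-0 scores are already scheduled.
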